#### Methods to handle protocol non-adherence and methods to handle missing data

As indicated above, all participants with a minimum of two study visits will be included in the primary analysis, therefore including participants even with incomplete data at every time point, a strength of using an AUC endpoint. There will be no imputations for missing data in the primary outcome. Secondary analyses will also be conducted in a per-protocol (PP) population including only participants with available data at all time-points and received the scheduled interventions. Protocol non-adherers will also be excluded in the PP analyses.

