### Trial design

CIRCUIT is an open-label, multicentre randomised clinical trial. Participants with a haematological malignancy or autoimmune/inflammatory disease will be randomised in a 1:1 ratio to receive either an additional COVID-19 booster pre-immunosuppression with a DT booster after 6 months of therapy or a DT booster pre-immunosuppression and an additional COVID-19 booster at 6 months. Participants at least 9 months post-BMT will be randomised in a 1:1 ratio to either receive a COVID-19 booster either following randomisation or after 6 months.

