#### Inclusion criteria

Adult aged ≥18 years with a medical condition included in table 1.Previously vaccinated with at least two doses of any licensed COVID-19 vaccine who requires initiation of moderate to severe immunosuppression; the most recent vaccination must have been given more than 3 months prior.Planned significant immunosuppressive therapy for at least 1 year (table 1).No cyclophosphamide, alemtuzumab or rituximab treatment in the past 5 years (concurrent corticosteroids with treatments listed in table 1 are permitted).Voluntary written informed consent.

**Table 1 T1:** Study populations

Group 1*	
**Haemato-oncology**	**Systemic autoimmunity**
Haematological malignancy (excluding bone marrow transplant recipients)† (n=40) B-CLL Follicular or marginal zone lymphoma Multiple myeloma Diffuse large B-cell lymphoma Other haemato-oncology condition at the discretion of the study PI or their delegate	ANCA-positive vasculitis,‡ ANCA-negative vasculitis,‡ Polyarteritis nodosa,‡ Churg-Strauss,‡ Ankylosing spondylitis,‡ Autoimmune hepatitis,§ IgG4 disease,‡ Inflammatory bowel disease,¶** Psoriatic arthritis,‡ Psoriasis, Rheumatoid arthritis,‡ SLE,‡ Sjogren’s syndrome,‡ Myasthenia gravis,†† Multiple sclerosis,‡‡ Autoimmune encephalitis, Neuromyelitis optica,¶ Bullous pemphigoid,¶ Pemphigus vulgaris¶ and variants, Sarcoidosis, Uveitis, other autoimmune/inflammatory conditions diagnosed by a specialist physician and at the discretion of the study PI or their delegate.
	B-cell depletion therapies, eg, rituximab, ocrelizumab, ofatumumab (n=40)
	Anti-metabolite therapies: azathioprine, calcineurin inhibitors, mycophenolate or methotrexate (moderate immunosuppression) (n=40)
	TNFα inhibition (with or without azathioprine or methotrexate or leflunomide to prevent anti-drug antibodies) (n=40)
	Cyclophosphamide or alemtuzumab (severe immunosuppression) (n=40)
	Janus kinase (JAK) inhibitors±leflunomide (n=40)
	Anti-IL-17 and/or 23 monoclonals, eg, secukinumab (n=40)

Group 2
*Bone marrow transplant (n=40)* Haematological malignancy—autologous or allogenic transplant (excluding for treatment of a primary immunodeficiency)

* Eligible patients with both a haematological malignancy and a systemic autoimmune condition are to be enrolled in the haematological malignancy sub-stratum.

† WHO criteria.

‡ EULAR criteria.

§ Biopsy proven.

¶ Mayo criteria.

** Crohn’s Disease activity index.

†† McDonnel I criteria.

‡‡ Must have AChR or Musk autoantibody positive.

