### Statistical methods

#### Statistical methods for analysing primary and secondary outcomes

Baseline participant characteristics will be summarised by randomised arm for each sub-stratum separately and combined. Primary analyses will compare immunogenicity endpoints between randomised arms on an intention-to-treat basis, that is comparing participants as randomised regardless of whether they received immediate or deferred vaccinations according to the protocol. Log_10_ NAb titres will be summarised at each time point and presented graphically within each stratum. The primary outcome will be time-weighted AUC change from baseline in anti-SARS-CoV-2 log_10_ NAb titre over 12 months. The primary analysis will follow a modified intention to treat approach (mITT) and include all randomised participants with a baseline visit and at least one post baseline time point measured. This approach allows for the inclusion of all participants, even with partial follow-up. The AUC will be calculated for each participant using the trapezoidal rule based on all available data. To assess for bias due to missing data, a secondary analysis which will only include patients who completed the study and have no missing data will be performed. These results will be compared with the mITT analysis. Additionally, if the proportion of patients with missing data is over-represented in one study arm, additional sensitivity analyses will be performed. Randomised arms will be compared within each treatment stratum separately using simple, unadjusted two-sample t-tests. In the event of unbalanced baseline characteristics, adjusted comparisons using linear regression methods may be performed. Results will be presented as mean differences, 95% CIs and p values. There will be no adjustment of p values and CIs for multiple comparisons across the seven sub-strata. In addition to analyses within strata, analyses combining all strata will be performed. Analyses will test for different effects of immediate versus deferred vaccination in separate strata by testing for interactions between strata and randomised arm. These results will be presented as forest plots, by strata and overall. Analysis for Group 2 participants will be presented independently using similar approaches as above as appropriate.

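### The per-protocol set requires data at every time-point, so it mixes missing data with non-adherence and largely repeats the completer analysis

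*Protocol article*

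**What the plan says.** The section on non-adherence and missing data (protocol article) states: "Secondary analyses will also be conducted in a per-protocol (PP) population". It defines that population as "including only participants with available data at all time-points and received the scheduled interventions" and adds: "Protocol non-adherers will also be excluded in the PP analyses". It does not define non-adherence.

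The primary analysis, described under the statistical methods for primary and secondary outcomes, is a modified intention-to-treat analysis that will "include all randomised participants with a baseline visit and at least one post baseline time point measured". As a check for bias from missing data, the same section says "a secondary analysis which will only include patients who completed the study and have no missing data will be performed". The non-adherence section itself counts the ability to use participants with incomplete data as an advantage of the AUC endpoint.

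**The concern.** A per-protocol analysis asks whether the result holds among those who followed the protocol. Whether every sample was obtained is a different question, and the completer analysis already covers it.

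Making complete data a condition of the per-protocol set has three consequences:

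- An adherent participant with one missed sample is dropped, although the time-weighted AUC can be computed without that sample.
- The set is selected on survival and full follow-up. The section on discontinuing or modifying the intervention lists progression of the underlying disease among the reasons for withdrawal, so those removed are unlikely to be a random subset.
- If the per-protocol and primary results differ, the reader cannot tell whether adherence or completeness caused it, because both change at once.

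**Working it through.** **How the three sets relate**

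| Set | Data condition | Adherence condition |
|---|---|---|
| Modified intention-to-treat (primary) | Baseline and at least one later value | None |
| Completers | Study completed, nothing missing | None |
| Per-protocol | Data at every time-point | Scheduled interventions received; non-adherers removed |

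The per-protocol set is in effect the completer set minus those who missed an intervention or were non-adherent. No row combines the primary analysis's data condition with an adherence condition.

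**The plan's own power figure.** The Sample size section gives an SD of 0.12 log10, a difference of 0.13 log10, a two-sided 5% level and 40 participants per sub-stratum. With 1:1 allocation that is 20 per arm. The noncentrality is 0.13 / (0.12 × √(2/20)) = 3.43 on 38 degrees of freedom, which gives power of 91.6% by the noncentral t (92.9% by the normal approximation). The stated figure of over 90% is reproduced.

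**Illustration of the completeness condition.** Inputs:

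- k = 8 required samples (assumption). The Data collection methods section gives eight visits for Group 1 after randomisation and the initial booster. It says blood is taken at baseline and at on-site follow-up visits, without saying how many of the eight are on site.
- Attendance a per visit, independent between visits (assumption; the article gives no rate).
- Loss to follow-up of 10% and mortality of 1% (Sample size section), so 0.89 remain.

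Fraction kept = a^8 × 0.89. Power is recomputed with the same SD and difference, with n per arm rounded.

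| a | a^8 × 0.89 | Kept of 40 | n per arm | Power |
|---|---|---|---|---|
| 0.98 | 0.851 × 0.89 = 0.757 | 30.3 | 15 | 81.7% |
| 0.95 | 0.663 × 0.89 = 0.590 | 23.6 | 12 | 71.8% |
| 0.90 | 0.430 × 0.89 = 0.383 | 15.3 | 8 | 52.3% |

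Before the 11% is removed, missed visits alone leave 85%, 66% and 43%, with power of about 86%, 76% and 58%. At 95% attendance, including the 11%, seven required samples would keep 62% and nine would keep 56%, so the exact count matters less than the attendance rate.

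**The case against.** Several points can be made for the plan.

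**The analysis is secondary.** The primary analysis keeps partial data, and its sample size and power do not change. This stands, and it limits the weight of the point.

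**The figures are hypothetical and concern single sub-strata.** This also stands. The plan includes analyses combining all strata. If 59% of the 280 in Group 1 remained, about 82 per arm, power on the same inputs would exceed 99%. The loss of precision matters within sub-strata; the selection and the mixing of two questions remain at any sample size.

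**The completer and per-protocol sets are not identical.** Completers include people who attended every visit but missed a vaccine. Comparing the two sets therefore says something about adherence, but only among those with complete data. They overlap; they are not duplicates.

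**Detail belongs in the analysis plan.** This is true of what counts as non-adherence. It is not true of the completeness condition, which the article states outright.

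**A stronger reading that the text does not support.** The Group 1 design has participants "receive either an additional COVID-19 booster pre-immunosuppression with a DT booster after 6 months of therapy", yet immunosuppression enters eligibility only as "Planned significant immunosuppressive therapy for at least 1 year". No stated per-protocol criterion mentions starting or staying on it. A reader might infer that the set keeps participants who never started or who stopped, in whom the before-versus-during contrast did not exist. The article does not say so. It excludes protocol non-adherers without defining them, and that term could cover these participants. The definition can properly be left to the analysis plan, which is not shown. Nor is this set the only place where exposure is examined: the secondary outcomes include responses by mode of immunosuppression employed and modelling of its effect on protection.

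**Conclusion.** The point holds for the completeness condition. As written, the per-protocol set excludes adherent participants for a single missed sample, selects on survival and full follow-up, and leaves no planned population defined by adherence alone.

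Under the assumptions above, some 15 to 30 of 40 participants per sub-stratum would remain, with power of about 52% to 82% instead of 91.6%. That range rests on eight required samples, independent attendance of 90% to 98% and the stated 11% loss or death. It describes a supportive analysis within single sub-strata. The article does not state whether Group 1 participants who never started or who stopped immunosuppression stay in the set, and no conclusion about them is drawn here. This is a modest defect in a secondary analysis, and it is cheap to correct.

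**What to change.** In the section on non-adherence and missing data:

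1. Remove the requirement for data at all time-points from the per-protocol definition.
2. Define the set by receipt of the scheduled vaccinations and absence of protocol non-adherence, with missed visits handled as in the modified intention-to-treat analysis. Name the vaccinations meant, because the Intervention and comparator section says the COVID-19 booster is not a study intervention, which leaves the reach of scheduled interventions unclear.
3. Keep the completer analysis as the separate check on missing data.
4. In the analysis plan, before data lock, list what counts as non-adherence. State whether not starting or stopping the planned immunosuppression is included for Group 1. Any analysis that conditions on therapy at week 24 selects on a post-randomisation state in an open-label trial, so it should be supportive only. It should also be limited to Group 1, since Group 2 compares times since transplant.

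The cost is a change of wording. Vaccinations and concomitant medication are already collected. The downside is that the per-protocol set will then include participants whose AUC rests on partial data, as the primary analysis already does.

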#### Data safety monitoring committee

The DSMB will comprise at least one biostatistician, one immunologist, one infectious diseases physician and either a haematologist, rheumatologist, gastroenterologist or neurologist. All DSMB members will be independent of the study, the Kirby Institute and UNSW and all agents who fund or support the trial. The DSMB chair will be selected by the members at the first meeting. The study statistician will have an ex-officio role on the DSMB but will not be a voting member.

The Terms of Reference and Operating Guidelines of the DSMB were drafted and finalised in collaboration with DSMB members prior to study commencement.

#### Interim analyses

An interim safety analysis of full summary data examining booster vaccine-associated AEs, vaccine-induced disease flares and breakthrough COVID-19 infections will be performed when 30% (100) of participants reach the 24-week time point. A second safety analysis and an efficacy analysis examining the primary endpoint will be performed when 50% (160) of participants have reached 12 months. Additional meetings at which full interim data summaries will be reviewed may be scheduled following the occurrence of repeated or unresolved clinical events such that the Co-ordinating Principal Investigator (CPI) and DSMB Chair feel a full interim safety summary is warranted, or if the first DSMB meeting indicates a further meeting is warranted prior to all participants completing the study.

DSMB meeting reports will include open and closed session reports. Open session reports will include data on study conduct, protocol compliance, recruitment, baseline and follow-up characteristics and will be distributed to the PSC Chair, study statistician and DSMB members. Outcome results will not be discussed at open sessions. Closed session reports will be provided as unblinded reports and distributed only to DSMB members who will discuss outcome results, make decisions and formulate recommendations.

Following each DSMB review of full safety data, the DSMB will recommend to the PSC through the PI to (a) continue the study without modification, or (b) continue with stated modifications, or c) terminate the study.

### Trial monitoring

Study monitoring will be conducted by routine on-site monitoring visits and by centralised monitoring to confirm the trial is being conducted according to the protocol and regulatory guidelines, to ensure participant safety and to maintain data integrity. Initial on-site monitoring visits will be conducted after five participants have been enrolled or approximately 3 months after recruitment start whichever comes first. Following the initial on-site monitoring visit, subsequent on-site visits will be conducted every 6 months and then at study closeout with centralised monitoring conducted on an ongoing basis during the trial. Sites that enrol a high number of patients over a short period of time (ie, have high recruitment rates), those with higher than expected failure rates, recruitment of ineligible patients, significantly higher or lower per participant AE/SAE rates or where there is an abnormal distribution of critical efficacy and safety data will have on-site monitoring every 6–8 weeks. The sponsor will submit an annual safety report to the central ethics committee for review and consideration.

## Ethics and dissemination

### Research ethics approval

The research protocol and related study documentation were approved by the Western Sydney Local Health District Human Research Ethics Committee on 25 August 2022 (Ref no. 2022/PID00782 – 20022/ETH0069). Following central ethics approval, participating sites sought approval from their local research governance body.

### Protocol amendments

Protocol amendments will also be submitted for approval by the central Human Research Ethics Committee and local research governance bodies. Following ethics approval, investigators will be informed in writing of all changes.

### Dissemination

Study results will be published in peer-reviewed medical journals and presented at local and international conferences. All findings regardless of the outcome will be reported; study data will be shared with other investigators and stakeholders on request. A lay summary of study findings will be prepared in the form of a participant letter and, following ethics approval, will be made available through the clinicians managing participants’ study qualifying medical conditions.
